#### Research hypothesis 2a

By 12 weeks after initiation of diet, participants in the modified Paleolithic diet group will have a clinically greater reduction, relative to the observation period, of perceived fatigue (assessed by FSS) than those in the low saturated fat diet group.

#### Research hypothesis 2b

By 12 weeks after initiation of diet, participants in the modified Paleolithic diet group will have clinically greater improvement, relative to the observation period, with respect to both motor function (gait, assessed by the timed 25-ft walk test [T25FW] and by the 6MWT; hand, assessed by 9-hole peg test (9HPT); physical activity outcomes, measured by accelerometer [e.g., increased daily steps, increased time spent in light-intensity activity, increased time spent in moderate-intensity activity, reduced time spent sedentary]; sleep quantity, as measured by accelerometer) and cognitive function (assessed by the SDMT-O) than those in the low saturated fat diet group.

#### Research hypothesis 2c

By 12 weeks after the initiation of diet, participants in the modified Paleolithic diet group will have clinically greater improvement, relative to the observation period, with respect to quality of life (assessed by Multiple Sclerosis Quality of Life 54 [MSQOL54] instrument) and mood (assessed by Hospital Anxiety and Depression Scale [HADS]) than those in the low saturated fat diet group.

#### Research hypothesis 3

After 24 weeks of the diet intervention, changes in the measures identified in hypotheses 1a and 1b observed at 12 weeks will be sustained in ≥ 80% of the participants in both diet groups.

### Study Design

This 36-week randomized parallel group clinical trial consists of three 12-week periods during which assessments of perceived fatigue, quality of life, motor and cognitive function, physical activity and sleep, diet quality, and social support for eating will be collected. The 12-week periods will consist of:*Observation*: Participants continue eating their usual diet.*Intervention*: Participants will be randomized to either the modified Paleolithic or low saturated fat diet for the intervention period. Participants will receive support by a registered dietitian (RD) through coaching telephone calls and emails.*Follow-up*: Participants will continue the study diet for an additional 12 weeks with minimal RD support to assess the ability of the participant to sustain the study diet on their own.

Study evaluations will be done to compare the effects of the two study diets on perceived fatigue (primary outcome measured by FSS) and secondary outcomes (cognitive function, motor function, QOL). The protocol was prepared according to the Standard Protocol Items: Recommendations for Interventional Trials (SPIRIT) guidelines (*see* Figs. 1 and 2 and Additional file 1: SPIRIT Checklist).

**Fig. 1 Fig1:**
[figure not shown]
Dietary Approaches to Treat Multiple Sclerosis-Related Fatigue Study flowchart. *MS* Multiple sclerosis *RRMS* Relapsing-remitting multiple sclerosis

**Fig. 2 Fig2:**
[figure not shown]
Standard Protocol Items: Recommendation for Interventional Trials (SPIRIT): the schedule of enrollment, interventions, and assessments. *SPMSQ* Short Portable Mental Status Questionnaire, *FSS* Fatigue Severity Scale, *9HPT* 9-Hole Peg Test, *T25FW* Timed 25-foot walk, *SDMT-O* Symbol Digit Modalities Test–Oral, *6MWT* 6-Minute walk test, *MSQ* Medical Symptoms Questionnaire, *MFIS* Modified Fatigue Impact Scale, *MSQOL54* Multiple Sclerosis Quality of Life 54, *FSMCF* Fatigue Scale for Motor and Cognitive Function, *MSIS v2* Multiple Sclerosis Impact Scale version 2, HADS Hospital Anxiety and Depression Scale, PSQI, *PSS 10* Perceived Stress Scale 10, *IPAQ-L* International Physical Activity Questionnaire–Long, SF36 36-Item Short Form Health Survey, *PDQ* Perceived Deficits Questionnaire, *MHI* Mental Health Inventory, FFQ Food Frequency Questionnaire

### Study setting

Data collection will be completed at the University of Iowa (UI) Preventive Intervention Center in Iowa City, IA, USA, by trained research assistants blinded to the group assignment. The medical monitor will be blinded to group assignment. Unblinding of assessors and medical monitors will not be permitted. To ensure that the proposed study is conducted without bias toward either of the study diets, [name] will not have access to study participants or raw study data and will not be involved in data analysis.

### Eligibility criteria

Adults with RRMS who can ambulate 25 ft with either no support or unilateral support, living within approximately a 500-mile radius of Iowa City, meeting eligibility criteria, and providing written informed consent will be invited to participate. The inclusion criteria are outlined below:a. Willing to allow their neurologist to sign a letter confirming MS diagnosis and criteria used to confirm diagnosisb. Definitive diagnosis of RRMS based on the revised 2010 McDonald criteria [36], confirmed by the treating neurologistFSS score ≥ 4 obtained within 12 weeks of scheduling their first study visit (Screened participants with FSS ≥ 3 and < 4 will be contacted again in 6 months to retake FSS to determine if they qualify, if participants desire.)Ability to shop for and prepare, or availability of someone in the family to shop for and prepare, home-cooked meals according to the study diet guidelinesWilling to keep detailed food records of all consumed foods and beveragesAged between 18 and 70 years at time of enrollment into the studyWilling to eat a diet that includes more vegetables and excludes many comfort foods such as those made with white flourWilling to eat a diet that eliminates red meat (beef, pork, lamb, veal), limits saturated fats (butter, coconut oil, margarine, and hydrogenated oils found in processed foods) to 15 g per day, and includes unsaturated fats (e.g., vegetable oils, nuts, fatty fish) to 20–50 g (4–10 teaspoons) per day if assigned to the low saturated fat diet but willing to eat saturated fats > 20 g per day if assigned to the modified Paleolithic dietNot pregnant or planning to become pregnant in the next 12 monthsAble to walk 25 ft without support or with only unilateral support (i.e., cane in one hand)Have not been told by a physician or other health care professional that they have celiac diseaseWilling and able to eat gluten-containing grainsLives within approximately a 500-mile radius of Iowa City, which includes Illinois, Indiana, Iowa, Kansas, Michigan, Minnesota, Missouri, Nebraska, Ohio, South Dakota, and Wisconsin

The exclusion criteria are outlined below:Taking insulin or warfarinHaving a relapse during the prior 12 weeks before consenting (The screening process will continue, with screening scheduled at least 12 weeks after the last relapse start date, if relapse happened after consenting; participation will be continued.)Undergoing treatment for cancer by radiation or chemotherapy within the prior 12 months other than for skin cancer (They will be contacted after the 12 months if participants desire.)Being diagnosed with kidney stones, heart failure, angina, or liver cirrhosisHaving a psychiatric disease, such as schizophrenia, that makes study adherence more difficult (Participants with depression and anxiety diagnoses are allowed.)Having a diagnosis of an eating disorder such as anorexia, bulimia, binge eating, or orthorexiaHaving BMI < 19 kg/m^2^Having a moderate to severe mental impairment as measured by the Short Portable Mental Status Questionnaire (SPMSQ) [37]Participating in another research study investigating MS or other medications, diet, supplements, exercise, or other treatmentsHaving had gastric bypass surgery with their treating physician believing it is medically unsafe to participate in this studyHaving been told by a physician or other health care provider they have celiac diseaseHave adverse physical reaction to eating gluten-containing productsLiving outside a 500-mile radius of Iowa CityNot able or willing to comply with the study protocol

Exclusion criteria for continuation into the intervention phase of the study are as follows:Inability to obtain blood at visit 1 or 2Not providing a sufficiently detailed visit 1 food recordNot mailing back visit 1 study materials by study day 28Not responding to queries for clarification of food record details within 7 days of the second attempt to contact

### Recruitment

Participants will be recruited from within a 500-mile radius of Iowa City. The North Central Multiple Sclerosis Society Region, which serves Iowa and Nebraska, has over 8000 members. The research team will work with the support groups of the National Multiple Sclerosis Society (NMSS) in communities within a 2-hour driving distance of Iowa City to advertise the study to their members. Additionally, the study team will work with regional MS centers, the North American Research Committee on Multiple Sclerosis (NARCOMS), the UI Hospitals neurology clinic, the Iowa City VA neurology clinic, the Swank Foundation, [name], and other organizations to recruit study participants.

### Randomization

Participants will be randomized to the modified Paleolithic or low saturated fat diet on the basis of the screening FSS score that qualified them for the study. Two randomization tables based on computer software will be used, one for moderate perceived fatigue (a score ≥4 and < 5.5) and the other for high perceived fatigue (≥ 5.5), so that similar mean FSS scores are achieved for each diet group. The randomization tables are accessible (password-protected) only by intervention dietitians.

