#### Nutrition counseling

Following randomization, participants will receive two in-person and five phone nutrition counseling sessions with the intervention RD. Personalized emails with feedback will be sent after participants return the diet checklists every 4 weeks. Participants may contact the intervention RD at any time to receive additional support. A final in-person counseling session will be conducted at visit 4. Nutrition counseling will be based on the Self-Determination Theory and use the Motivational Interviewing (MI) communication approach [39–43]. The dietitians providing the intervention will be screened for MI aptitudes prior to being hired, and they will receive training in this area prior to study initiation. The dietitian will also receive ongoing consultative support throughout the study from an RD who is a member of the Motivational Interviewing Network of Trainers (MINT). A lesson plan was developed to guide the counseling session for each in-person study visit. Participants will be asked to consent to being audio recorded during in-person nutrition counseling sessions at visits 2 and 3. The visit 2 audio recordings will be reviewed by the MINT RD to verify fidelity to the study diet guidelines, which consist of explaining the recommended and not recommended foods for the intervention diet and rationale for key dietary components. The MINT RD will review all visit 2 audio recordings and 20% of visit 3 audio recordings using the OnePass instrument [44] to assess use of the MI approach. A mean OnePass score ≥ 4 indicates average competence in MI.

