### Assessments and visit schedule

#### Visit 1 – week 1

Participants will fast for 12 hours prior to visit 1. Eligibility criteria will be checked, and the participant will be consented (Additional file 4: Appendix 3). Height and weight will be measured to confirm a BMI ≥ 19. If participants qualify for the study, their vital signs will be measured, and fasting blood will be drawn. Questionnaires including a medication audit and motor and cognitive testing will be completed, as listed in Fig. 2, and personal information such as duration of MS and handedness will be recorded. Participants will be instructed on how to (1) keep a 3-day food record and use a loaned food scale for weighing the amount of food eaten, (2) complete an FFQ, and (3) wear an accelerometer.

Participants will complete questionnaires, as listed in Fig. 2, via a secure Research Electronic Data Capture (REDCap) system at home 1–3 days after the study visit. Participants will wear an accelerometer for 7 continuous days (24 h/d) following this visit and record the foods, beverages, and dietary supplements consumed between Thursday and Saturday following visit 1. The accelerometer and dietary forms will be returned by mail.

#### Visit 2 – week 12

Participants will wear an accelerometer for the 7 days prior to visit 2 and will record the foods, beverages, and dietary supplements consumed between Thursday and Saturday prior to the visit. Participants will complete questionnaires (as outlined in Fig. 2) 1–3 days prior to visit 2 using REDCap. Participants will fast for 12 hours prior to visit 2. Vital signs, blood, motor and cognitive tests, and questionnaires will be completed at visit 2 (*see* Fig. 2). Food records, FFQs, and accelerometer data, will be reviewed for completeness. Participants will be randomized to one of the study diets.

The study participant and their family member(s) or adult companion will meet with an RD who will provide individualized nutrition counseling on the participant’s assigned study diet. The family/adult companion will be advised that, during our previous studies, we have observed that the study participants who have had their families adopt the study diet along with the study participants have had greater levels of success with adopting and sustaining the intervention diets. The family/adult companion will be advised that they are expected to be supportive of eating study-compliant foods.

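### The intervention dietitians alone hold the randomization tables, so as written allocation is not concealed from the staff who assign and deliver the diets

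*Protocol article*

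**What the plan says.** **Custody.** The Randomization section of the protocol article says: "The randomization tables are accessible (password-protected) only by intervention dietitians". No other holder, sealed envelope or stepwise release is described.

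**Form of the sequence.** The same section says "Two randomization tables based on computer software will be used, one for moderate perceived fatigue" and the other for high perceived fatigue (4 to below 5.5, and 5.5 or above). Participants are allocated "on the basis of the screening FSS score that qualified them for the study".

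**Timing and contact.** Under Assessments and visit schedule, visit 2 (week 12) includes a completeness review of food records and accelerometer data, followed by "Participants will be randomized to one of the study diets". At that visit the participant and family "will meet with an RD who will provide individualized nutrition counseling on the participant’s assigned study diet". Under Nutrition counseling, once randomized, "participants will receive two in-person and five phone nutrition counseling sessions with the intervention RD".

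**Decisions before randomization.** The end of the Eligibility criteria section lists four grounds for not continuing into the intervention phase. One of them is not "providing a sufficiently detailed visit 1 food" record.

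**Stated protections.** Study setting blinds the data-collecting research assistants and the medical monitor, and keeps one individual away from participants, raw data and analysis. Data analysis specifies a masked statistician.

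**The concern.** Random allocation protects the comparison only if nobody who can influence a participant's entry knows which treatment comes next. Here the role with sole custody of the lists is also the role that delivers the interventions. Two features make this more than a formality. First, about 12 weeks pass between consent at visit 1 and randomization at visit 2, with continuation decisions in between. Second, the Discussion expects some participants to drift towards the diet they were not given, so perceived fit with a diet is something dietitians can be expected to notice.

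If knowledge of the next diet affected who was randomized, or when, the arms could differ in motivation, likely adherence or expected response. The primary outcome, the Fatigue Severity Scale (FSS), is self-reported by participants who know their diet, so it is sensitive to such differences. Adjusting for measured baseline variables would not reliably remove them.

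**Working it through.** The point rests on how the sections fit together. The plan gives no figure to reproduce.

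**1. Who makes the assignment?** Only the dietitians can open the tables, so they must be the ones who read off each assignment.

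**2. Do they also deal with participants?** Yes. The intervention dietitian gives the counseling, and a dietitian meets the participant at the randomization visit. The text places this counseling after assignment.

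**3. Is the relevant table known in advance?** Yes. The stratum is fixed by the screening FSS score, obtained before visit 1.

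**4. Is there discretion before assignment?** The four continuation criteria are:

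| Criterion | Nature |
|---|---|
| Blood obtained at visits 1 and 2 | Objective |
| Visit 1 materials mailed by study day 28 | Dated rule |
| Queries answered within 7 days of the second contact attempt | Dated rule |
| Visit 1 food record detailed enough | Judgement |

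Three are objective and one is a judgement. The article does not say who makes that judgement or when. The completeness review at visit 2 also names no one.

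**5. Do the stated protections close the gap?** The password restricts access to the dietitians and hides nothing from them. Blinding of assessors and medical monitor addresses measurement and safety review. Masking of the statistician addresses analysis. None of these conceals the sequence from the dietitians.

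**6. What could the bias amount to?** The document gives no basis for a value, so the following is an assumed range only. Suppose k of the 34 analysed participants in one arm are there through selective placement, and each differs by 1.0 FSS point in expected outcome. That is about one SD, since √((0.9² + 1.1²)/2) = 1.005 from Table 4. The arm mean then shifts by k/34. The standard error of the difference is √((0.9² + 1.1²)/34) = 0.244. The two-sided false-positive rate is P(|Z + shift/0.244| > 1.96).

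| k | Shift (k/34) | Share of the 0.7 target | False-positive rate |
|---|---|---|---|
| 1 | 0.029 | 4% | 5.2% |
| 3 | 0.088 | 13% | 6.5% |
| 5 | 0.147 | 21% | 9.3% |
| 8.5 | 0.25 | 36% | 18% |

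The SDs are Table 4's between-group values at the last visit, not SDs of change, so the rates are approximate even under the assumption. The last row needs 8 or 9 of 34 participants selectively placed, which is hard to reach through one food-record judgement.

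**7. Can a change still help?** The target is 2 × 45 = 90 participants, and Trial status reports 58 consented. At least 90 − 58 = 32 of those planned had not yet been consented. Some of the 58 may also have been awaiting visit 2.

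**The case against.** The strongest reply is that a gatekeeping role for the dietitians is inferred. No section says that they screen, consent, judge food records, schedule visit 2 or decide continuation. Data collection belongs to blinded research assistants, and counseling follows randomization. Three of the four continuation criteria leave little room for discretion. The visit 1 record is due by day 28, so if it is judged on receipt, about eight weeks of other participants' randomizations may intervene before this participant's row is reached. Access to tables does not prove that later rows are visible. Release procedures are also the kind of detail a condensed article leaves to its full protocol. Finally, closing the tables to everyone else serves a purpose, because it protects the blinding of assessors and statistician.

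Most of this stands, and it limits the claim. A reader might infer that dietitians can steer participants by rejecting records or rescheduling visits. The document does not show this. A reader might also infer that any selection passes undiminished into the FSS comparison. That is too strong, because stratification by screening FSS and an outcome defined as change from the observation period partly deal with differences in fatigue level.

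The reply does not remove the core. The article is not silent on custody. It names the holder, and that holder is the treatment provider. Wanting to keep assignments from assessors does not require giving the lists to the dietitians.

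**Conclusion.** The point holds in limited form. As written, allocation is not concealed from the staff who make the assignment and deliver the diet, and no stated safeguard covers this. That conclusion needs only the custody sentence and the description of the dietitians' role.

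Whether the gap could be exploited depends on two matters the article leaves open: whether dietitians have a part in continuation decisions, and whether they can see rows ahead of the current one. The risk of selection bias is therefore avoidable but of unknown size, and would work mainly through expected response or adherence. The range shown above is conditional on assumed values and estimates nothing about this trial. In particular, an 18% false-positive rate should not be quoted as a finding. The document gives no evidence that any assignment was influenced.

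**What to change.** Take the tables out of the dietitians' hands. Load the two stratum lists into a concealed allocation function, for example in the REDCap system the trial already uses, or give them to someone with no participant contact. Release each assignment to the dietitian singly and with a time stamp, only after a different staff member has recorded that all continuation criteria are met. State in the protocol who judges the food record and when. Report how many participants were randomized before and after the change, so that readers can see what share of the sample was exposed.

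The cost is a short amendment and a one-off system set-up, with no extra visits. It cannot reach participants already randomized.

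If later rows are already hidden and other staff decide continuation, no change of procedure is needed. The custody sentence in the Randomization section should then be corrected to say so.

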### Intervention

#### Study diets

The study diets are summarized in Table 1.

**Table 1 Tab1:** Study diets

	Modified Paleolithic (Wahls Elimination Diet)	Low Saturated Fat (Swank Diet)
Recommended	• 2–3 cups (6 cups raw) leafy greens/day • 2–3 cups sulfur rich vegetables/day • 2–3 cups colorful fruits/vegetables/day • 6–12 oz. meat, fish, poultry or game/day • Approved fats (Extra virgin olive oil, coconut oil/butter, ghee, avocado, flax, hemp, walnut, sesame and sunflower oil, tahini, rendered animal fats and bacon grease)	• 2 cups vegetables/day • 2 cups fruit/day (fresh preferred) • 2 cups fat-free dairy/day • 4 servings grain and cereal/day (whole preferred) • 4 oz. + skinless chicken/turkey breast, white fish or shellfish/day • 4–10 tsp. (20–50 g) unsaturated fat/day
Encouraged or Limited	• 12 oz. organ meat/week • 16 oz. omega-3 fish/week • 1 serving seaweed, algae, nutritional yeast/day • 1 serving fermented food/day • Maximum 4 oz. nuts and seeds/day (soaked preferred) • Maximum 2 tbsp. flax, hemp and/or walnut oil/day • Flax and chia seeds to achieve 2 soft bowel movements/day • Maximum 1 alcoholic beverage/day (women) • Maximum 2 alcoholic beverages/day (men) • Maximum 1 tsp. approved sweetener/day (honey, molasses, maple syrup, stevia or sugar)	• Maximum 3 egg yolks/week • Maximum 3 cups caffeinated beverages/day • Maximum 1 alcoholic beverage/day • Maximum 15 g saturated fat/day • Maximum 50 g unsaturated fat/day
Not Recommended	• Dairy products (cow, goat, mare, soy milk, rice milk) • Grains with gluten • Gluten-free grains • Eggs • Legumes (beans, peas, soy, lentils, peanuts) • Nonallowed sweeteners; approved sweeteners > 1 tsp. per day • Nightshade vegetables/spices during first 12 weeks on diet • White fruits/vegetables (apple, pear, white potato) • Vegetable oils (corn, soy, canola, palm kernel, cottonseed, grapeseed), partially hydrogenated • Monosodium glutamate • Irradiated, deep fried, or microwaved food	• Red meat (beef, pork, lamb, veal, liver, kidney, heart, tongue) • Chicken or turkey dark meat • Rabbit, venison, elk, squab, pheasant • Dairy products with > 1 g saturated fat per serving • Foods containing hydrogenated fat or > 1 g saturated fat per serving such as desserts, snacks, candies, etc. • Butter, margarine, shortening, coconut oil and other saturated and hydrogenated fats
Supplements	• 1 tsp. cod liver oil • 1000 μg methyl B_12_ • 1000 μg methylfolate • 5000 IU vitamin D_3_^a^ • 1 multivitamin/mineral tablet for men aged 50+ without iron	• 1 tsp. cod liver oil • 1000 μg methyl B_12_ • 1000 μg methylfolate • 5000 IU vitamin D_3_^a^ • 1 multivitamin/mineral tablet for men aged 50+ without iron

^a^Dose adjusted based on serum vitamin D

##### Study diet 1

The modified Paleolithic diet stresses more vegetables than other Paleolithic diets that have been studied previously, and it limits meat to 6–12 oz per day. Like other Paleolithic diets, it excludes all grain, legumes, and dairy (except for clarified butter or ghee) and additionally excludes eggs. Nightshade vegetables/spices will be excluded during the first 12 weeks on the diet and then reintroduced during the second 12 weeks on the diet, if the participant desires, to safely test tolerance to nightshades while under study team observation. Specific guidance will be provided to participants about how to reintroduce nightshades into the diet.

##### Study diet 2

The low saturated fat diet restricts saturated fat to ≤ 15 g per day and limits unsaturated fat to 20–50 g (4–10 teaspoons) per day. (This diet is promoted by the Swank MS Foundation [38] and includes more emphasis on vegetables and whole grains than the original Swank Diet.)

